			***Treatment***			
	*Intake*	*B1*	*Evaluation*	*PT1*	*F1*	*F2*
**Mini International Neuropsychiatric Interview (M.I.N.I.)** [69] ***(clinical diagnosis of psychiatric disorders)***	X					
**Sociodemographics**	X					
**Current Medications and Therapies **	X			X	X	X
**Quick Inventory of Depressive Symptomatology Self-Report (QIDS-SR)** [70] ***(Self-reported Severity of Depressive Symptoms)***	X	X	X	X	X	X
**Montgomery-Åsberg Depression Rating Scale (MADRS)** [78] ***(Clinician-rated Severity of Depressive Symptoms)***		X		X		
**Morningness-Eveningness Questionnaire (MEQ)** [86] ***(Chronotype – Morningness/Eveningness preference)***	X				X	
**Ultra Short Munich Chronotype Questionnaire (µMCTQ)** [87] ***(Chronotype – Sleep Timing)***	X	X		X	X	X
**Pittsburgh Sleep Quality Index (PSQI)** [84] ***(Subjective Sleep Quality)***		X		X	X	X
**Insomnia Severity Index (ISI)** [85] ***(Severity of Insomnia Symptoms)***		X		X	X	X
**Short Form Health Survey - 12 items (SF-12)** [82] ***(Health-related functional outcomes)***		X		X	X	X
**Mental Health Quality of Life (MHQoL)** [83] (***Quality of Life related to Mental Health***)		X		X	X	X
**Credibility/Expectancy Questionnaire (CEQ)** [71] ***(Treatment credibility and participant expectations)***		X				
**Adverse Event Scale** ***(Occurrence and severity of adverse events)***			X			
**Young Mania Rating Scale (YMRS)** [96] ***(Symptoms of (hypo)mania)***			X			

This table gives an overview of the questionnaires utilized at various assessment points in the Baseline, Treatment, and Follow-up. Each questionnaire’s purpose is indicated alongside the time points at which it was administered indicated with an X. No questionnaires are administered during melatonin assessments (M1, M2, M3) or MRI sessions (MRI-1, MRI-2)

### Actigraphy

To assess sleep patterns and circadian rhythm parameters, participants wear a medical grade actigraphy watch, the MotionWatch 8 (CamNtech, Cambridge, UK), throughout the treatment period, baseline week, and post-treatment week. This validated medical device contains an internal accelerometer that reliably captures movement data in 30-s epochs. Participants receive clear instructions on how to wear the watch and are encouraged to keep it on during all the waking and sleeping hours to ensure accurate and continuous data collection.

### Personal Illuminance Sensor

Participants wear a small, box-shaped light sensor developed by the Eindhoven University of Technology [88] near their clavicle from waking to bedtime during the baseline, treatment, and follow-up weeks to assess their light-related behaviors. This device uses a TAOSTCS34725 optical sensor and an onboard EEPROM memory of 64 kb. The sampling window is set to 30 s, meaning the device takes a light measurement every 10 s and averages these for the time window. To ensure optimal data collection, participants are instructed to turn the sensor upside down at bedtime to prevent it from measuring light exposure that does not actually fall on the eyes. Additionally, participants are advised to remove the sensor in wet conditions, as it is not water-resistant.

### Ecological Momentary Assessment (EMA)

Momentary affect states, momentary energy levels, and subjective sleep parameters are assessed using an ecological momentary assessment (EMA) approach in a subsample of 120 participants. Throughout the baseline, treatment, and post-treatment weeks, participants receive eight EMA notifications daily via a mobile application called M-Path [97]. Each notification, which takes approximately 1 min to complete, occurs at semi-random intervals across eight 105-min periods throughout the day. Participants have the flexibility to choose their preferred notification schedule, receiving alerts either between 7:00 AM and 9:00 PM, 8:00 AM and 10:00 PM, or 9:00 AM and 11:00 PM. To increase the validity of the momentary states, notifications become inaccessible 30 min after they are sent. In addition to the eight momentary notifications, participants are asked to complete a sleep diary each morning to assess subjective sleep parameters, as well as an evening questionnaire assessing daytime sleep, caffeine and drug intake, and treatment adherence.

### Melatonin assessments

In a subset of participants (*n* = 72), salivary melatonin samples are collected in three additional evening sessions: two during the measurement week before baseline (M1 – DLMO and M2 – Light Sensitivity), and one in the week following treatment (M3—DLMO). Participants collect saliva samples at home by swabbing a cotton swab in their mouth and placing it in a salivette®. Samples will be promptly refrigerated and shipped to the lab within 3 days. In the lab, samples are centrifuged and stored at − 20 °C for analysis. Melatonin concentration in the saliva samples is analyzed in the lab of Chrono@Work B.V. (Groningen, The Netherlands) with a double-antibody radioimmunoassay (RIA) (Direct Saliva Melatonin kit, NovoLytiX GmbH, Switzerland). Specific saliva sampling procedures depend upon the type of assessment (DLMO or Light Sensitivity).

#### Dim Light Melatonin Onset (DLMO) assessment

DLMO is assessed at M1 and M3. Participants provide eight saliva samples on each collection day, starting 4 h before their habitual sleep onset time (determined from the sleep diary in the baseline) and ending 1 h after. The samples are collected at hourly intervals, with two extra collections 30 min before and after habitual sleep onset. To ensure a dim light environment, participants are instructed to keep their home lighting as dim as possible and reduce the intensity and contrast of computer and phone screens to a minimum. Participants are also asked to sit away from Lamps, maintain a distance of at least 3 m from the TV, and close curtains.

#### Light Sensitivity

To evaluate light sensitivity, we estimate the light-induced melatonin suppression during baseline (M2). Five salivary melatonin samples are collected by the participants at 30-min intervals, beginning 1 h before habitual sleep onset and concluding 1 h after. Participants remain in the same lighting conditions as in the DLMO assessment, but 30 min before their habitual sleep onset time they are exposed to 30 min of light with an illuminance of approximately 250 lx at eye level and at distance of approximately 70 cm from a modified BLT lamp.

### Brain imaging

Sixty participants at LUBEC undergo two brain imaging sessions at the 3 Tesla MRI facility of the Leiden Institute for Brain and Cognition (LIBC) of the Leiden University Medical Center (LUMC) in Leiden. The First MRI session takes place the week before BLT, and the second session is conducted the week after BLT completion. Each session has a maximum duration of 60 min (including preparation, positioning of participant, and scanning). The brain scans are performed on a Philips 3 T MRI system (Best, The Netherlands) at the Leiden Institute for Brain and Cognition (LIBC) of the Leiden University Medical Center (LUMC) in Leiden, The Netherlands. The following MRI imaging sequences are used in each session:*Structural High-Resolution T1*: This sequence captures detailed information about GM, including parameters like THK, VOL, SA, and LGI. It is also essential for subsequent functional scan analysis. For this, we will use a high-resolution T1 weighted image with the following parameters: repetition time (TR) = 7.9 ms, echo time (TE) = 3.5 ms, flip angle = 8°, field of view (FOV) = 250 × 195.83 × 170.5 mm, 155 slices.*Diffusion Weighted Imaging (DWI)*: This sequence enables the assessment of the brain’s structural connectivity by examining the primary WM tracts. Data from the DWI is analyzed using a diffusion tensor imaging technique (DTI). For this, we use a DTI high-iso sense sequence with the following parameters: TR = 6500 ms, flip angle = 90°, FOV = 224 × 224 × 125.4 mm, number of slices = 57, shim size = 100 × 100 × 100. SENSE = 2.5. Diffusion-sanitizing gradient encoding is applied in 32 directions with a diffusion weighted factor of b = 1000 s/mm^2^ and two b0 (b = 0) images. Images are acquired parallel to the anterior–posterior commissure.*Functional Resting State*: This sequence provides information about the functional connectivity of brain networks while at rest. For this, a T2*-weighted using gradient-echo planar imaging (EPI) sequence is used. The parameters entail: TR = 2200 ms, TE = 30 ms, flip angle = 80°, number of slices = 40 transverse, slices thickness = 2.75 mm, FOV = 22 × 220 × 120.725.*Structural T2w Image*: To better reconstruct the structural images and obtain exact values of THK, VOL, SA, and LGI within the analysis program FreeSurfer (http://surfer.nmr.mgh.harvard.edu/), we also perform a structural T2-weighted 3D Flair Image at the end of the scan with the following parameters: TR = 4800 ms; FOV = 250 × 250 × 182,56; 326 slices.

### Plans to promote participant retention and complete follow-up {18b}

An interactive feedback session is planned with the participants during the post-treatment assessment where we evaluate their individual study outcomes, focusing mainly on the EMA data. This offers a personalized incentive for continued participation. Online questionnaires and automated reminders are integrated to ensure data retention. Additionally, personal contact with participants is maintained throughout the study to promote adherence to the protocol.

### Confidentiality {27}

Information collected about participants during this clinical investigation is treated confidentially. The collection and processing of participants’ personal information is limited to what is necessary to ensure the study’s scientific practicability, the evaluation of efficacy, adherence, side effects, and the investigational product’s safety. All data is pseudo-anonymized using participant identification numbers.

### Plans for collection, laboratory evaluation and storage of biological specimens for genetic or molecular analysis in this trial/future use {33}

Saliva will be collected from the participants that consent to the melatonin assessments. Melatonin concentration in saliva will be analyzed in the lab of Chrono@Work B.V. (Groningen, The Netherlands) and destroyed afterwards. Saliva cannot be used in future studies.

## Statistical methods

### Statistical methods for primary and secondary outcomes {20a}

This analysis plan provides the initial framework for examining primary and secondary outcomes. A significance level of 0.05 will be applied unless otherwise specified, with corrections for multiple comparisons (e.g., Bonferroni) used when necessary. All analyses will follow the intention-to-treat principle, accounting for the nested structure within centers if appropriate. The analyses outlined here may be subject to minor modifications based on advancements in the field. Should any deviations from the original plan occur, these will be clearly documented and justified. Our reporting will adhere to the guidelines set by the CONSORT statement [98].

### Study Sample Description

We will report the descriptive statistics of socio-demographic and clinical variables for the whole sample, per site, and per treatment arm. In specific analyses involving subsamples (e.g., melatonin assessments, EMA, and MRI), we will provide socio-demographic and clinical characteristics of the subsample and report any distinctions from the overall sample*.*

### Primary Study Outcome – Clinical Improvement between Treatment Conditions

To compare the three different BLT administration strategies in terms of clinical improvement (measured as the difference in MADRS scores between baseline and post-treatment assessments), we will employ a multilevel mixed-effects modelling approach. MADRS scores will serve as the dependent variable, with a fixed effects for timepoint (*pre- and post-treatment*), and the interaction between timepoint and treatment arm (*Light@Home, LightCafé*, and* LightCafé* +). Random intercepts for participants and study centers will be included to account for individual differences and center-level variability, but only if they improve model fit, as determined by evaluation of the Akaike Information Criterion (AIC) and Bayesian Information Criterion (BIC). Random slopes for time within participants will also be considered and included based on the same criteria. Socio-demographic (age, sex) will be evaluated for potential confounding effects, similar to the credibility and expectancy of the treatment arms as assessed with the CEQ. The primary analysis will focus on the interaction between timepoint and treatment arm to determine whether clinical improvement differs across the three BLT strategies. Furthermore, multilevel logistic regression will be used to test differences in response (yes/no) and remission (yes/no) between treatment arms using the same structure and procedure as above.

### Secondary Study Outcomes

#### Subjective Assessment of Depressive Symptoms, Relapse Rates and Functional Outcomes

Multilevel mixed-effects models will be constructed to assess depressive symptom improvement, measured weekly during therapy and at follow-up assessments using the QIDS-SR scores as the dependent variable. Fixed effects will include timepoint as an categorical variable (baseline, 1 week, 2 weeks, 3 weeks, 4 weeks, 10 weeks, and 4 months), and the interaction between timepoint and treatment condition (*Light@Home*,* LightCafé*, and *LightCafé* +). Random intercepts and slopes will be included for participants and study centers, as well as random slopes for time within participants, based on model fit criteria. Confounding variables (age, sex, clinical diagnosis, and credibility/expectancy of treatment) will also be evaluated and included as necessary. A variable will be added to account for treatment duration (1 week, 2 weeks, 3 weeks). Similar models will be considered for analyses of relapse rates, functional outcome, and Quality of Life with inclusion of the respective timepoints as fixed effects (see Table 1).

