### Intervention description {11a}

In all study arms, participants are subjected to BLT in adherence to Dutch BLT guidelines [72], utilizing an Innolux LED light Lamp delivering light with an illuminance of 10,000 lx at a distance of 70 cm and a color temperature of 3800 K. BLT sessions, lasting 30 min each, are scheduled from Monday to Friday between 7:30 AM and 10:30 AM.

The number of BLT sessions is contingent upon the individual response of each participant, with a maximum duration of 3 weeks. Initially, participants undergo five consecutive BLT sessions during the workweek. Subsequently, the therapeutic efficacy is evaluated utilizing the QIDS-SR during the Friday session. If the QIDS-SR falls below 6, remission is inferred, leading to the termination of BLT. Alternatively, an additional five sessions are administered. This evaluation and decision process is repeated at the end of the second week. If the QIDS-SR score is still above 6, a third and final week of treatment is provided.

This individualized strategy is intended to reduce the small risk of (hypo)manic switches, which occur in less than 2% of bipolar patients and almost exclusively in those not maintained on mood stabilizers [11, 73]. We will continuously monitor for (hypo)manic symptoms using the Young Mania Rating Scale (YMRS; [74]) and clinical observation: a YMRS score ≥ 13 and clinician‐identified symptoms will lead to immediate treatment cessation, while scores of 10–11 will prompt a joint review with a second clinician to decide on discontinuation [75, 76].

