### Criteria for discontinuing or modifying allocated interventions {11b}

Participants can withdraw from the study at any time without providing a specific reason. BLT is discontinued upon the patient achieving remission or exhibiting mania symptoms as per the YMRS or clinical assessment. Furthermore, treatment discontinuation can be initiated by clinical staff when they consider it to be in the best interest of the patient.

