### Treatment phase

During the treatment phase, participants receive 1, 2, or 3 weeks of BLT within their assigned condition. Every Friday, depressive symptoms are assessed using the QIDS-SR, regardless of whether the participant received treatment that week. Treatment will be continued as long as QIDS-SR-score is higher than 6, with a maximum of 3 weeks. Treatment tolerability and mania symptoms are assessed using the YMRS after each week of BLT. EMA, actigraphy, and light logger usage continue throughout the treatment.

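### The QIDS-SR arm comparison is to be adjusted for treatment duration, a post-randomisation result set mainly by the QIDS-SR itself; this can shrink a real early arm difference

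*Protocol article*

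**What the plan says.** The section on subjective depressive symptoms, relapse and functional outcomes plans a multilevel model "using the QIDS-SR scores as the dependent variable", covering baseline, weeks 1 to 4, week 10 and month 4. Its fixed effects are categorical timepoint "and the interaction between timepoint and treatment condition"; no separate main effect of condition is listed. Age, sex, diagnosis and expectancy enter only where needed. Duration enters without condition: "A variable will be added to account for treatment duration (1 week, 2 weeks, 3 weeks"). Whether it is a main effect, interacts with time or varies over time is not stated. For other outcomes the article says "Similar models will be considered for analyses of relapse rates, functional outcome, and Quality of Life".

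Duration follows from the Friday score. Intervention description {11a}: "If the QIDS-SR falls below 6, remission is inferred, leading to the termination of BLT". Treatment phase: "Treatment will be continued as long as QIDS-SR-score is higher than 6, with a maximum of 3 weeks". Section {11b} adds mania symptoms and withdrawal as reasons to end treatment, and says that "treatment discontinuation can be initiated by clinical staff". Outcome measurement goes on after stopping: "Every Friday, depressive symptoms are assessed using the QIDS-SR, regardless of whether the participant received treatment that week".

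The Statistical methods section {20a} applies intention to treat to all analyses. The primary MADRS model lists no duration term.

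**The concern.** The week-1 and week-2 QIDS-SR values are outcome rows in this model, and they also largely determine one of its covariates. If an arm brings more patients to remission early, it will contain more one- and two-week patients. Holding duration fixed then compares arms within groups formed by early response, and part of the arm's benefit can be credited to the duration term. Such a comparison is no longer protected by randomisation. Duration is also part of what is being compared: Trial design {8} describes each strategy as lasting 1 to 3 weeks according to response. At stake are the self-rated depression trajectories and, if built the same way, relapse, function and quality of life.

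**Working it through.** **Plan figures.** The article gives no QIDS-SR mean, SD or effect, so there is no figure on this point to reproduce. The nearest is N = 210 for the MADRS. With noncentral F, df 2 and 207, and λ = 0.25² × 207 = 12.94, power is 0.902, so 210 reproduces. It is not affected by this point. The arm size used below is 231/3 = 77.

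**What the algebra says.** Let duration enter as a time-constant main effect, with D its dummies and γ their coefficients.
- Arm difference read at visit t: adjusted = raw(t) − γ·(mean D in arm 1 − mean D in arm 0).
- Change contrast, visit t minus baseline: the same γ-term is subtracted at both times and cancels. With complete data and the arms free at baseline, the change contrast is exactly unchanged.
- If the arms share a baseline, or duration interacts with time, the cancellation fails.

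**Simulation (all QIDS-SR inputs assumed).** Two arms of 77; visits at weeks 0, 1, 2, 3, 4, 10 and 16; baseline SD 3.5; SD of individual improvement 4; error SD 2; full arm effect 2 points; scores rounded and limited to 0–27. Duration is 1 if week 1 is below 6, 2 if week 2 is below 6, and 3 otherwise. Random-intercept GLS, 800 replicates, complete data. Entries are the week-4 arm effect, with the ratio to the unadjusted estimate in brackets (from unrounded values).

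| Scenario | No duration term | Main effect, change contrast | Main effect, read at week 4 | Main effect, common baseline | Duration × time |
|---|---|---|---|---|---|
| A: baseline 14, mean improvement 4.5 | −1.87 | −1.87 (1.00) | −1.37 (0.73) | −1.70 (0.91) | −1.65 (0.88) |
| B: baseline 12, improvement 4.5 | −1.75 | −1.75 (1.00) | −1.16 (0.66) | −1.50 (0.86) | −1.49 (0.85) |
| C: baseline 14, improvement 8 | −1.62 | −1.62 (1.00) | −1.03 (0.63) | −1.37 (0.84) | −1.42 (0.88) |
| D: baseline 13, improvement 8, faster | −1.52 | −1.52 (1.00) | −0.67 (0.44) | −1.09 (0.72) | −1.15 (0.76) |
| E: as A, arm effect only after week 3 | −1.87 | −1.87 (1.00) | −1.88 (1.01) | −1.88 (1.00) | −1.88 (1.01) |
| F: no arm effect, improvement 8 | −0.01 | −0.01 | −0.02 | −0.01 | −0.01 |

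Monte Carlo standard errors are 0.018 to 0.027.

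**Side effect of the harmless coding.** The baseline arm coefficient it implies is the week-4 reading minus the change contrast: A, −1.37 + 1.87 = 0.50; B, −1.16 + 1.75 = 0.59; C, −1.03 + 1.62 = 0.59; D, −0.67 + 1.52 = 0.85. Randomised arms with no true baseline difference would be shown 0.5 to 0.85 points apart, with the better arm looking worse.

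**The case against.** The strongest reply is that the simplest reading does no harm to the contrast that matters. The section describes a repeated-measures model of improvement and mentions no duration-by-time term. One person-level main effect cancels from change from baseline. This is correct, and it stands for that contrast.

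It does not rescue the choice. The listed terms are timepoint and its interaction with condition, without a condition main effect. Taken literally, either the interaction coefficients are arm differences at each visit, or the arms share a baseline. Both attenuate an early effect. Even the harmless coding distorts the adjusted arm means, and no coding tested improves the arm comparison.

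Other parts of the reply also stand. Duration is mainly, not wholly, set by the QIDS-SR. The MADRS response and remission models take the structure of the primary model, which has no duration term, and the time-to-remission analysis lists only age, gender and diagnosis. For relapse, function and quality of life, similar models are only under consideration.

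A reader might infer that the comparison is bound to be biased toward no difference, or that a fixed share of the effect is lost. The article supports neither, because it does not fix how the term enters. Regressing a single week-4 score on arm, baseline and duration retains 64–93% under its own assumed values, but that is not the planned model and should not be quoted as this trial's loss.

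**Conclusion.** The point holds in a limited form. The plan commits to adjusting the QIDS-SR arm comparison for a post-randomisation variable derived largely from that same outcome, which is at odds with its stated intention-to-treat principle. In scenarios A to D the week-4 arm effect retained is 44–73% (read at the visit), 72–91% (common baseline) or 76–88% (duration by time). It is 100% for the change contrast under a single time-constant main effect with arms free at baseline and complete data. Attenuation needs an arm effect that appears before the week-1 and week-2 decisions; in scenario E, where it comes later, nothing is lost. No scenario produced a false difference or moved the estimate away from no difference. The percentages rest on assumed QIDS-SR values; the classification of duration as a result of treatment does not. The primary analysis is untouched, so this is a modest flaw in secondary analyses.

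**What to change.** Delete the duration sentence, and state that no model used to compare arms (QIDS-SR, relapse, SF-12, MHQoL) contains treatment duration. Report the distribution of duration by arm descriptively, and leave speed of remission to the planned time-to-remission analysis. If a duration-adjusted model is still wanted, label it exploratory and not a randomised comparison. The cost is one or two sentences, with no change to data collection or sample size.

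Separately, Intervention description {11a} and Treatment phase treat a score of exactly 6 differently. Because that score decides duration, the passages must be reconciled before duration is tabulated.
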